***Main outcome measures***

In this study, we will examine the extent of adverse events related to the use of PDL cells. In addition to the safety assessment, the main outcome measure in the study protocol is the magnitude of change in the alveolar bone height (primary outcome for efficacy).

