***Evaluation of adverse events***

The investigators will record any adverse event with the exact name, onset date, severity, provided treatment and date of disappearance.

Each adverse event will be graded for severity using the following scale and criteria as outlined by the Ministry of Health and Welfare of the Chinese Government.

- **Mild**: The subject can continue the subsequent schedule without any treatment.
- **Moderate**: The subject can continue the subsequent schedule with treatment.
- **Severe**: The subject cannot continue the subsequent schedule.

The investigators will determine the relationship of the adverse event and the investigational cells.

The investigators will determine whether or not the adverse event is classified as a serious adverse event. A serious adverse event is defined as any experience suggesting a significant hazard, contraindication, side effect, or precaution. A serious adverse event includes any adverse experience resulting in any of the following outcomes:

- Death
- A life-threatening adverse experience
- Impatient hospitalization or prolongation of existing hospitalization
- A disability/incapacity that may interfere with the subject's daily life
- An adverse experience leading to a disability/incapacity
- A serious adverse experience at the same level as the above conditions
- A congenital anomaly/birth

**Efficacy assessment** [34,35]

The main outcome measure in the study protocol is change in the alveolar bone height at 3, 6, and 12 months post-operation. We set the rate of increase in alveolar bone height as the most statistically important outcome (primary outcome). The clinical attachment level (CAL), probing depth (PD), and gingival recession (GR) are generally used to assess pathology in periodontal disease. These parameters do not directly assess the efficacy of cells in periodontal tissue regeneration and were selected in the present study as secondary outcome measures to ascertain whether cells would cause abnormal periodontal healing following periodontal surgery. These measurements will be recorded at baseline and 12-months post-surgery.

***Standardized radiography and dental CT for regions of investigation*** [34,35]

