Our geometrically standardized radiography employs dental film (Kodak InSight Super Poly-Soft; Eastman Kodak Company, New York, USA) and photograph indicators (Cone Indicator-II; Hanshin Technical Laboratory, Hyogo, Japan) that are customized with resin stents. Two doctors specializing in dental radiology from the Department of Oral Diagnosis at Fourth Military Medical University School of Stomatology will measure the changes in the alveolar bone height (%) using the methods described below (Figure 2). Each examiner blinded to the treatment conditions will independently measure this value, and the median of 2 measurements taken from the same image will be selected for analysis. In addition, a dental CT that reports data automatically will be used to assess bone regeneration in selected cases. These data will be used for information purposes only or as a reference for the design of subsequent trials (not included in the analysis of this trial).

[figure not shown]

**Figure 2**. Schematic illustration of the bone regeneration assessment using standardized radiography. Points C, A and B represent the cementoenamel junction, apex and bottom of the bone defect, respectively. The examiner measured the tooth axis heights between Points C and A and between Points C and B (bone-defect depth, BDD) on the X-ray for each patient. To adjust for slight errors due to imaging, the measurements from 5 examiners were multiplied by the A-C ratio of the before to after administration to correct for C-B after administration. Based on C-B data before surgery and during follow-up (3, 6 and 12 months), increse of BDD was calculated to serve as an indicator of increase in alveolar bone height post-operation [37,38].

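### The Figure 2 legend, the only computing rule given for the primary outcome, has its direction reversed, gives no denominator for the percentage, and disagrees with the text on the number of readers

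*Protocol*

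**What the plan says.** **Points and distances.** The Figure 2 legend, under Standardized radiography and dental CT in the Efficacy assessment, fixes the landmarks: "Points C, A and B represent the cementoenamel junction, apex and bottom of the bone defect, respectively". The examiner measures C to A, and also the distance "between Points C and B (bone-defect depth, BDD) on the X-ray for each patient".

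**Correction for imaging differences.** Follow-up readings are "multiplied by the A-C ratio of the before to after administration to correct for C-B after administration".

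**Direction.** The legend then states that "increse of BDD was calculated to serve as an indicator of increase in alveolar bone height post-operation".

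**Scale.** Main outcome measures says that "the main outcome measure in the study protocol is the magnitude of change in the alveolar bone height", without a unit. The Efficacy assessment says: "We set the rate of increase in alveolar bone height as the most statistically important outcome (primary outcome". The radiography text expresses the change as a percentage and refers to Figure 2 for the method.

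**Visits.** The Efficacy assessment says: "The main outcome measure in the study protocol is change in the alveolar bone height at 3, 6, and 12 months post-operation". It does not name one of the three as primary.

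**Readers.** The radiography text has two dental radiology doctors reading independently, with the median of their two values analysed. The legend says that "the measurements from 5 examiners were multiplied by the A-C ratio of the before to after administration".

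**Analysis.** The Statistics section tests changes in clinical examination indices by repeated-measures analysis of variance, at p<0.05. It does not state sidedness and does not name bone height, a primary visit or a primary contrast.

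**The concern.** C is a landmark on the tooth and does not move with healing. B is the floor of the defect, and bone fill brings it towards C. So C-B is a depth that falls as bone is gained, while the legend reads its increase as gain. A programmer who coded the legend as it stands would report filling teeth as negative and deteriorating teeth as positive, and the between-arm difference would carry the wrong sign.

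The legend also has to supply the percentage that the text promises, and as written it does not: it ends at a change in C-B. Two analysts could follow the Protocol faithfully and report different percentages from the same films. The reader conflict affects the same variable, because it leaves open how many readings are combined into each value. All this falls on the outcome that carries the efficacy claim, in about 40 teeth.

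**Working it through.** The Protocol gives no effect size, standard deviation, power or result for this outcome, so there is no stated figure to reproduce. The lengths below are assumptions for illustration; the formulas come from the Figure 2 legend.

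**1. Direction**

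Corrected follow-up C-B = measured follow-up C-B × (A-C before / A-C after).

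Increase of BDD = corrected follow-up C-B − baseline C-B.

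Assume baseline C-B = 8 mm, baseline A-C = 14 mm, and a later film magnified by 5%, so that follow-up A-C = 14 × 1.05 = 14.7 mm.

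| True change | True C-B after | C-B on film (× 1.05) | Corrected (× 14/14.7) | Increase of BDD |
|---|---|---|---|---|
| 2 mm fill | 6.0 | 6.30 | 6.0 | 6.0 − 8.0 = −2.0 mm |
| 1 mm fill | 7.0 | 7.35 | 7.0 | 7.0 − 8.0 = −1.0 mm |
| 1 mm loss | 9.0 | 9.45 | 9.0 | 9.0 − 8.0 = +1.0 mm |

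The legend's quantity is exactly the negative of the bone change. The A-C correction removes the magnification, but it is a ratio of two positive lengths and cannot turn the sign round.

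**2. Percentage**

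The legend's two lengths give at least three possible denominators. For the same 2 mm fill:

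- baseline C-B: 2/8 = 25.0%
- baseline A-B (bone height from the apex, 14 − 8 = 6 mm): 2/6 = 33.3%
- C-A: 2/14 = 14.3%

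Even with baseline C-B fixed as denominator, a 2 mm fill is 40.0%, 28.6% or 22.2% for an assumed baseline of 5, 7 or 9 mm. Millimetres and percentages therefore cannot be read across teeth as the same result.

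**3. Readers**

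Two readings and readings from five examiners cannot both describe the same measurement. For two values the median equals the mean, so the choice between those summaries does not matter. The count does.

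**4. Visits**

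If each of the three visits were tested at two-sided 0.05 and any one could be claimed, the chance of a false positive would be 1 − 0.95³ = 14.3% for independent visits. By simulation it is 12.5%, 10.9% and 8.4% at assumed between-visit correlations of 0.5, 0.7 and 0.9. With one named visit, or one overall test, it is 5%.

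**The case against.** **The reversal is probably a slip.** The sentence that contains it also says the quantity stands for an increase in bone height, and the Efficacy assessment names an increase in bone height as the outcome. The intended direction is therefore clear. A two-sided test, or the overall F test of an analysis of variance, gives the same p-value either way. This stands. A reader might infer that the trial's headline result must come out with the wrong sign; the documents do not support that. They show that the written rule, applied literally, reverses the direction.

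**There are not two rival scales.** A reader might infer that millimetres compete with a percentage. No section gives millimetres for this outcome. The wording in Main outcome measures carries no unit and fits a percentage, and the two places that specify a scale agree on a relative one. This stands. What is missing is the denominator. The Figure 2 drawing is not reproduced in the text at hand, so a formula might appear there; the legend gives none.

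**The visits need not inflate type I error.** A reader might infer that a positive trial could be declared on whichever visit succeeds. The Protocol nowhere says so. It names a repeated-measures analysis, and one overall test would not inflate the error. A primary visit or contrast may also be fixed in a statistical analysis plan that is not shown. This stands, so the percentages in the fourth step are conditional and are not a defect shown in the Protocol.

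None of these objections makes the computing rule correct as written, supplies the denominator, or reconciles two readers with five.

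**Conclusion.** The point holds as an error in how the primary outcome is defined. By the Protocol's own landmarks, an increase of BDD is bone loss, and the stated correction cannot change that. The size is a full reversal: every millimetre of fill scores as minus one millimetre. The direction of the estimate, and so the arm judged better, depends on someone noticing. The p-value does not, provided the test is two-sided, which the Protocol does not state.

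The percentage is underdefined. In the assumed example the same fill ranges from 14.3% to 33.3% across the plausible denominators. That range rests on the assumed 8 mm and 14 mm and would differ for other teeth; the ambiguity itself rests on the legend's text. The reader counts contradict each other outright.

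The unnamed primary visit is a request for clarification only.

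**What to change.** 1. Replace the last sentence of the Figure 2 legend with a formula: bone gain = baseline C-B − follow-up C-B × (A-C at baseline / A-C at follow-up), where a positive value means gain.
2. Keep the percentage as the primary scale, as the Efficacy assessment and the radiography text have it, and state its denominator, for example 100 × bone gain / baseline C-B. Report the change in millimetres as supportive. Align the unitless wording in the Abstract and in Main outcome measures.
3. State the same number of readers, and the same rule for combining their readings, in the text and in the legend.
4. As a clarification, name the primary visit or contrast. Twelve months matches the length of follow-up and the timing of the secondary outcomes; 3 and 6 months would then be supportive.

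Items 1 to 3 change wording only: the C-B and A-C measurements are already planned, and no new films or visits are needed. The denominator should be chosen before any unblinded analysis, since choosing it afterwards would leave the result open to selection. Item 4 costs the option of leading with an earlier visit.

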***Inspection of periodontal tissue around the teeth under investigation***

We will measure the items shown below at 6 positions (mesiobuccal, buccal, distobuccal, mediolingual, lingual, and distolingual) around each tooth under investigation.

- Clinical attachment level (CAL): A stent will be prepared for each subject. Using the cementoenamel junction or the margin of the restorative material as the control point, the distance between the control point and bottom of the gingival sulcus will be measured for each test subject using the same periodontal probe.
- Probing depth (PD): Simultaneously with the CAL measurement, we will measure the distance from the gingival margin to the bottom of the gingival sulcus for each subject using the same periodontal probe
- Bleeding on probing (BOP; + or -): The presence of bleeding will be checked 10 s after probing.
- Gingival index (GI): The GI will be determined as described by Löe and Silness [36]
- Mobility of tooth (MO): MO will be determined as described by Miller [37].
- Recession of gingiva (REC): Using the cementoenamel junction or the margin of the restorative material as the control point, the distance between the control point and gingival margin was measured for each subject using the same periodontal probe
- Plaque index (PlI): The PlI will be determined as described by Silness and Löe [38].
- Width of keratinized gingiva (KG): The shortest distance between the coronal gingival margin and the mucogingival junction will be measured for each subject using the same periodontal probe.

**Statistics**

This study will be performed using a per-protocol analysis. In this analysis, all of the randomized teeth will receive at least one therapy, but teeth that do not receive treatment will be excluded (modified per-protocol analysis). The last-observation-carried-forward method will be used for the per-protocol analysis. The missing data points will be input into the post-baseline follow-up visits from the last observation available for each patient. For analysis, we will use SAS version 8.2 software (SAS Institute Inc., Cary, North Carolina, USA). The per-protocol set analysis will be performed for the primary outcome. The baseline between-group comparisons within age and clinical examination indices will be performed using independent group *t* tests. The between-group comparison of sex will be performed using Fisher’s exact probability test. The changes in clinical examination indices will be tested using a repeated-measures analysis of variance. The level of statistical significance will be set at *p*<0.05.

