**Study Design**

Each patient will be examined by at least five independent principal investigators. Investigator 1 will perform a basic oral examination using a clinical inspecting apparatus and X-ray, check all of the inclusion and exclusion criteria, and ensure that the informed consents are signed by the patients at the Registration Center. Next, Investigator 2 will perform the pre-surgical treatments, re-check the inclusion and exclusion criteria, and extract the tooth/teeth that will be subjected to cell isolation by Investigator 4. Investigator 2 will select no more than 2 teeth (from different regions) to be investigated in each patient. Following the collection of baseline data from the selected tooth/teeth by Investigator 3, Investigator 4 will culture the cells, make the cell products, and create an allocation table consisting of 2 cases per block that will be allocated to the Control group (Bio-oss® only) and Cell group (Bio-oss® and cell sheets). According to this allocation table, a label indicating the corresponding group will be attached to each tooth; thus, each tooth will be randomly assigned to one of the two treatment groups. The maximum number of teeth from one patient will be 2. Hence, if one tooth is allocated to the Control group, the other will be automatically assigned to the Cell group. However, if a patient only has one tooth chosen for investigation, it has a fair chance of being allocated to either group. Once a tooth is assigned to a group, it will be kept in a secure locked drawer inaccessible to all other study personnel. All of the patients will receive oral hygiene instructions, a tooth cleaning and basic dental therapies if needed, such as cavity filling and occlusal adjustment. The periodontal surgery will be performed 4-5 weeks after these pre-surgical treatments. When the oral condition and cell products are both ready for surgery, Investigator 4 will be asked to give the assigned implants (Bio-oss® only or a combination of Bio-oss® and cell sheets) to the physician (Investigator 5), who will then perform the surgery. This procedure ensures that the randomization is not influenced by the physicians taking part in this study. Investigator 4 will record the patients’ details and number the envelope assigned to each tooth. Investigator 3 will perform the follow-up study (data collection, safety assessment, etc.) of the patient, and the blind will not be broken until this clinical trial is completed.

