***Inclusion criteria***

- those 18 years old and <65 years old;
- those diagnosed with a 2- or 3-walled vertical intrabony defect 3 mm deep from the top of the remaining alveolar bone from radiography and clinical periodontal parameters;
- those who have accomplished the initial preparation and shown good compliance;
- those with a mobility of Degree 2 or less for the tooth under investigation and with a width of the attached gingiva for which the existing GTR and bone graft implantation treatments are considered appropriate;
- those for whom supportive periodontal treatment is applicable (the tooth has the potential to be maintained for at least 3 years) and in accordance with the usual post-operative procedures following flap operation and GTR treatment;
- those whose oral hygiene is well established and who are able to perform appropriate tooth brushing and cleaning following instructions from the investigators and/or sub-investigators after investigational drug administration;
- those who have at least one tooth (e.g., wisdom tooth) that needs to be extracted due to impacted or non-functional reasons and who agree to the tooth extraction;
- those who understand the purposes of the trial and are capable of making an independent decision to comply with trial requirements.

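### The only analysis planned for the primary outcome drops randomised teeth that go untreated, and such losses could differ between the Cell and Control groups

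*Protocol*

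**What the plan says.** The Statistics section sets the principle for the whole study: "This study will be performed using a per-protocol analysis". For the main endpoint it adds: "The per-protocol set analysis will be performed for the primary outcome". No all-randomised, full-analysis or sensitivity set is named anywhere in the protocol.

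One sentence defines the set. Its first half states that "all of the randomized teeth will receive at least one therapy"; its second half states that "teeth that do not receive treatment will be excluded (modified per-protocol analysis". Missing follow-up visits are filled by last observation carried forward within this set.

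On the order of events, the Study Design section says: "Investigator 4 will culture the cells, make the cell products, and create an allocation table consisting of 2 cases per block". The unit is the tooth: "each tooth will be randomly assigned to one of the two treatment groups". A patient contributes at most two teeth, and two teeth from one patient go to opposite groups. Later in the same section: "When the oral condition and cell products are both ready for surgery, Investigator 4 will be asked to give the assigned implants", and this covers both kinds of implant. Under Inclusion criteria, every patient must be among "those who have at least one tooth (e.g., wisdom tooth) that needs to be extracted due to impacted or non-functional reasons", whichever group that patient's teeth enter.

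**The concern.** The Abstract poses a superiority question. For that question the comparison protected by randomisation is between all teeth as assigned. A set defined by whether treatment was given depends on something that can happen after randomisation.

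Here that event need not be equally likely in the two groups. A Control tooth needs Bio-oss and the membrane procedure. A Cell tooth needs these and also successful isolation, subculture and sheet formation. If a tooth is assigned and its sheet then cannot be used, the exclusion rule can remove it for a reason that has no counterpart in the Control group. If patients whose cells grow poorly also heal differently, the remaining teeth are no longer comparable. In a two-tooth patient, losing one tooth also breaks the within-patient pair.

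Investigator 4 cultures the cells, makes the products and creates the allocation table. On the protocol's description, the person best placed to judge whether a sheet is usable therefore knows the assignment, which makes selective loss harder to rule out afterwards.

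**Working it through.** The protocol states no power, effect size, SD, dropout rate or culture-failure rate, so there is no figure to reproduce. The check has three parts.

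**1. What the text fixes**

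| Question | What the protocol says |
|---|---|
| Set for the primary outcome | Per-protocol, no other set named |
| Are all randomised teeth treated? | Yes in the first half of the defining sentence; the second half provides for teeth that are not |
| Is culture success required before assignment? | Not stated; culture is listed before the allocation table, but implants are called assigned before the products are said to be ready |
| What happens to a Cell tooth without a sheet? | Not stated |

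The culture steps are stated as 7-10 days to first confluence, about 20 days of subculture and about 10 days for the sheet. In sequence that is 7 + 20 + 10 = 37 to 10 + 20 + 10 = 40 days, or about 20 + 10 = 30 days if the 20 days include the primary culture. Surgery is placed 4-5 weeks, or 28-35 days, after the pre-surgical treatments. If extraction coincides with those treatments (an assumption), the sheet is ready within the surgical window on the shorter reading and after it on the longer one. A missing sheet is therefore not a remote possibility.

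**2. Layout**

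About 40 teeth in about 30 patients, with at most 2 each, gives 40 − 30 = 10 two-tooth patients and 30 − 10 = 20 one-tooth patients. Blocks of 2 give about 20 teeth per group.

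**3. Illustrative size**

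Let k be the number of Cell teeth dropped (assumed 1 to 5) and g the mean difference, in SD, between retained and dropped teeth (assumed 0.5 or 1). Teeth are treated as independent.

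- Shift in the Cell mean = (k/20) × g
- SE of the group difference = √(1/20 + 1/(20 − k)) SD

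| k | Cell teeth left | SE (SD) | Shift, g = 0.5 | Shift / SE | Shift, g = 1 | Shift / SE |
|---|---|---|---|---|---|---|
| 1 | 19 | 0.320 | 0.025 | 0.08 | 0.05 | 0.16 |
| 2 | 18 | 0.325 | 0.05 | 0.15 | 0.10 | 0.31 |
| 3 | 17 | 0.330 | 0.075 | 0.23 | 0.15 | 0.45 |
| 4 | 16 | 0.335 | 0.10 | 0.30 | 0.20 | 0.60 |
| 5 | 15 | 0.342 | 0.125 | 0.37 | 0.25 | 0.73 |

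In the last row a shift of 0.73 SE would raise the two-sided 5% error rate to P(Z > 1.96 − 0.73) + P(Z < −1.96 − 0.73) = 0.109 + 0.004, about 11%.

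The loss of precision is minor. The difference detectable with 80% power, (1.96 + 0.84) × SE, is 0.89 SD with 20 v 20 teeth, 0.94 SD with 20 v 16 and 0.96 SD with 20 v 15. The issue is comparability more than power.

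**The case against.** A reader might infer that unusable sheets remove teeth from the Cell group alone and can never remove a Control tooth. The protocol does not support that, for three reasons.

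- Study Design lists culture and product preparation before the allocation table. If that is the true order, a failed culture falls before randomisation and biases neither group.
- The same section makes readiness of the cell products a condition for handing over either kind of implant, and every patient must have a donor tooth. A failed culture could therefore hold back a Control tooth too, including the paired one.
- The rule drops only teeth that receive no treatment. A Cell tooth operated on without a sheet has arguably been treated and might stay in.

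The set is also narrower than its label suggests. The Statistics section lists no exclusion for deviations or incomplete follow-up, so as written it is close to all treated teeth.

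These points stand as limits on the mechanism, but they do not remove the defect. The text settles none of the three readings. On the first, implants are still described as assigned before the products are ready. On the second, randomised teeth are still lost because of the culture result, in an unstated pattern. On the third, a reader applying the per-protocol label would usually remove the tooth, and the protocol does not say which applies.

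It is also tempting to say that the bias favours cells. That requires poor cell growth to predict poor healing, which the protocol does not state. Nor is feasibility, mentioned in the Abstract, lost: an efficacy set does not prevent sheet failures from being reported. A separate analysis plan could add other sets, but the protocol itself fixes this one for the primary outcome.

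**Conclusion.** The point holds in a limited form. The protocol commits the primary outcome of a superiority comparison to a single set that leaves out randomised but untreated teeth, and the sentence defining the set contradicts itself. Because only Cell teeth need a usable sheet and the timing of assignment relative to culture success is unclear, exclusions could differ by group, plausibly more often in the Cell group.

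The size and direction of the bias are not known. The range of 0.025 to 0.25 SD rests entirely on assumed failure counts, an assumed prognosis gap and losses confined to Cell teeth. The largest case is about 0.7 SE, and with 3 teeth lost and a 0.5 SD gap it is under a quarter of an SE. Independence of teeth is also assumed; positive correlation between two teeth of one patient would shrink the SE and raise these ratios somewhat, but the protocol gives no correlation.

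**What to change.** 1. In the Statistics section, make the primary analysis all randomised teeth in the group assigned, whatever was implanted. Keep the treated or per-protocol set as a sensitivity analysis.
2. State how teeth without post-operative radiographs enter the analysis. A tooth never operated on has no post-operative measurement, and carrying its baseline forward would score it as no change. One option is a likelihood-based model using the available 3-, 6- and 12-month visits, with a sensitivity analysis that varies the assumed outcome of untreated teeth.
3. Reconcile the two halves of the sentence that defines the set.
4. Report exclusions and sheet failures by group and reason.
5. In Study Design, state that a patient's assignment is opened only after that patient's cell products are recorded as ready, so that culture failure falls before randomisation. How a failed culture is managed clinically is for the sponsor to reconcile across the sections.

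The cost is mainly wording, plus a change in when the assignment is opened. If cells are not already cultured for every patient, which the protocol leaves unclear, it also means culture for the one-tooth patients later assigned to Control, about half of 20. Statistically, Cell teeth that did not receive cells would dilute the effect slightly, and teeth with no outcome data need an assumption that must be stated and tested.

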**Fourth Military Medical University**

**2011.06**

**Abstract**

**Background**: Periodontitis, which progressively destroys tooth-supporting structures, is one of the most widespread infectious diseases and the leading cause of tooth loss in adults. Evidence from animal studies indicates that stem cells derived from either bone marrow or the periodontal ligament (PDL) can be used in therapies for the regeneration of lost or damaged periodontal tissues. The aim of this clinical trial is to identify the safety of the clinical use of stem cells in periodontal therapy and to verify whether stem cells in combination with Bio-oss® are more effective than Bio-oss® alone in guided tissue regeneration (GTR) techniques for treating periodontal disease in human patients.

**Methods/Design**: In this protocol, we designed a single-center randomized trial to treat periodontal disease using GTR techniques and bovine-derived bone mineral (BDBM, Bio-oss®) with or without the incorporation of autologous periodontal ligament stem cells (PDLSCs). In total, approximately 30 periodontitis patients aged 18 to 65 years with a total of approximately 40 test teeth with periodontal intrabony defects and who satisfy our selection and exclusion criteria will be enrolled. These patients will be randomly assigned to either the Cell testing group (treatment with GTR and PDLSC sheets in combination with Bio-oss®) or the Control group (treatment with GTR and Bio-oss® without containing cells). During a 12-month follow-up, we will examine the extent of any adverse events related to the use of PDL cells. Moreover, the primary outcome is the magnitude of change in the alveolar bone height, and the secondary outcome measures are improvements in clinical attachment level (CAL), probing depth (PD), and gingival recession (GR).

**Discussion**: The results of this trial will assess the efficacy, safety and feasibility of using autologous PDLSCs to treat periodontal intrabony defects, and these data will provide primary clinical evidence for the future use of autologous stem cells in regenerative periodontal therapy.

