**Patients and enrolment**

Patients with periodontitis visiting our dental institution will be requested to participate. This study will be conducted in compliance with Good Clinical Practice guidelines. Prospective patients who provide written informed consent will undergo clinical inspection and an oral cavity diagnosis. We will then select approximately 30 patients (approximately 40 testing teeth) who satisfy the selection and exclusion criteria described below (most of these criteria were chosen from previous similar periodontal clinical trials [34,35]).

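### CAL, PD and GR have only a baseline and a 12-month reading, so the planned repeated-measures ANOVA amounts to a change-score test: valid, but less efficient than adjusting for baseline

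*Protocol*

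**What the plan says.** The Abstract states that "the secondary outcome measures are improvements in clinical attachment level (CAL), probing depth (PD), and gingival recession (GR"). The Efficacy assessment section repeats that status and then fixes their timing: "These measurements will be recorded at baseline and 12-months post-surgery". Three follow-up readings are planned only for the primary outcome, "change in the alveolar bone height at 3, 6, and 12 months post-operation".

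The Statistics section gives one sentence on how the clinical indices are tested: "The changes in clinical examination indices will be tested using a repeated-measures analysis of variance". It names no model term as the treatment test and no baseline covariate. Baseline values enter only through a separate comparison of the groups: "The baseline between-group comparisons within age and clinical examination indices will be performed using independent group" t tests. The significance level is p<0.05, with sidedness not stated.

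On size and allocation, Patients and enrolment says "We will then select approximately 30 patients (approximately 40 testing teeth"), and Study Design has Investigator 4 "create an allocation table consisting of 2 cases per block". A patient may contribute up to two teeth, and two teeth of one patient go to opposite groups.

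**The concern.** Repeated-measures ANOVA is usually chosen for a series of follow-up readings. Here the series has two members, and the first is taken before treatment. Two consequences follow.

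- The group-by-time term reduces to a comparison of raw changes. That fixes the weight on baseline at 1, whereas the best weight is the regression slope, which equals r when the SDs are equal. Power is lost whenever r is clearly below 1.
- A chance baseline difference D between the groups shifts the expected change difference by −(1−r)D. With about 20 teeth per group and no stratification by defect severity stated, such differences are to be expected. A baseline t test detects some of them but corrects none.

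At stake is the precision of the three secondary outcomes in a trial of about 40 teeth. A further, smaller matter is that a two-visit ANOVA also prints a group main effect, and the text does not rule it out as the treatment test.

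**Working it through.** The protocol gives no power, effect size, SD or correlation, so there is no figure of its own to reproduce.

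**Inputs from the protocol.** Two readings per tooth (Efficacy assessment); about 40 teeth, taken as 20 per group; alpha 0.05, taken as two-sided.

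**Assumptions.** Equal SD at both times; teeth independent; true 12-month difference 0.9 SD; r varied. The 0.9 SD is close to the 0.886 SD that a 12-month-only comparison of 20 v 20 would detect with 80% power, since (1.960 + 0.842) × √(2/20) = 0.886.

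**Step 1: what the ANOVA tests.** On a simulated 2-group by 2-time data set of 40 teeth, the group-by-time F was 6.0635, equal to the squared t on the change score. The group main effect F was 0.6077, equal to the squared t on the mean of the two visits.

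**Step 2: variances per tooth, in SD² units.**
- Change score: 2(1−r)
- ANCOVA: 1−r²
- Ratio: (1−r²) / [2(1−r)] = (1+r)/2

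**Step 3: power.** The noncentrality is 0.9 / √(2V/20), with 38 df for the change score. For ANCOVA, V is multiplied by 1 + 1/36 for estimating the slope, with 37 df.

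| r | V change | V ANCOVA | ratio | noncentrality, change | power, change | noncentrality, ANCOVA | power, ANCOVA |
|---|---|---|---|---|---|---|---|
| 0.3 | 1.40 | 0.91 | 0.65 | 2.41 | 65% | 2.94 | 82% |
| 0.5 | 1.00 | 0.75 | 0.75 | 2.85 | 79% | 3.24 | 88% |
| 0.7 | 0.60 | 0.51 | 0.85 | 3.67 | 95% | 3.93 | 97% |
| 0.8 | 0.40 | 0.36 | 0.90 | 4.50 | 99.2% | 4.68 | 99.5% |

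In teeth, at r = 0.5 and a difference of 0.886 SD (normal approximation), 80% power needs 15 per group with ANCOVA and 20 with the change score.

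**Step 4: where the gain ends.** Setting 2(1−r) = (1−r²)(1 + 1/36) gives 1+r = 72/37, so r = 0.946. Above that, ANCOVA's variance is the larger, by less than 1/36, or 2.8%.

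**Step 5: validity.** In simulation (40,000 runs per setting), type I error was 4.8% to 5.2% for all tests. With a true difference of 0.886 SD, the change score and ANCOVA both averaged about 0.89.

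**Step 6: the group main effect.** It estimates half the difference, 0.45 SD, with variance (1+r)/2 = 0.65, 0.75, 0.85 and 0.90. Power is 41%, 36%, 32% and 31% at r = 0.3, 0.5, 0.7 and 0.8.

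**The case against.** **The text asks for a test of changes, and that is the group-by-time term.** This stands. A reader might infer that the plan halves the treatment effect, because the group main effect would. The documents do not support that: the sentence speaks of testing changes, and a main effect that averages pre- and post-treatment values tests no change. The powers in Step 6 describe a misuse that the wording fails to exclude, not the plan. Naming the term could also be left to an SAP.

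**What remains is efficiency, and its size rests on an unstated r.** This also stands. The gain is about 17 points at r = 0.3, 9 at 0.5, 2 at 0.7 and under 1 at 0.8. Chance baseline imbalance is not an extra bias on top of this: over repeated randomisations it is the same variance loss, already counted in (1+r)/2.

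**These outcomes were chosen mainly to detect abnormal healing.** The Efficacy assessment section does say that they do not directly assess the efficacy of the cells, so power to show a 0.9 SD benefit is not what the trial turns on. That limits the weight of the point. It does not remove it: the Abstract frames them as improvements, and a tighter interval serves a healing check as well.

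**The calculation ignores paired teeth.** This is correct. With 30 patients and 40 teeth, 40 − 30 = 10 patients contribute two teeth, one in each group. The figures treat all teeth as independent and are not the power of a model with a patient effect.

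**The argument might seem to extend to bone-defect depth.** It does not carry over unchanged. That outcome has three follow-up readings and is analysed as a percentage change, so it needs its own model.

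**Conclusion.** The concern holds in a limited form and for the secondary outcomes only. With two readings, the planned repeated-measures ANOVA on its natural reading is a raw change-score test: valid and unbiased, but less efficient than adjusting for a baseline already collected. The variance ratio (1+r)/2 needs only equal SDs. The power figures also need 20 v 20 independent teeth and a 0.9 SD difference. The benefit is worthwhile at r of 0.3 to 0.5 and negligible from about 0.8. That the treatment term is unnamed is a wording risk to close, not evidence that the main effect is intended. The point is an improvement worth making; it does not put the trial's primary conclusion in doubt.

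**What to change.** In the Statistics section, for CAL, PD and GR, replace the repeated-measures ANOVA sentence with wording such as:

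*The 12-month value will be analysed in a linear model with treatment as factor, the same tooth-level summary at baseline as covariate, and a patient random effect to account for patients with two teeth. The adjusted treatment difference will be reported with its 95% confidence interval.*

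State which tooth-level summary of the six probing positions is used, identically at both times. If the ANOVA is kept, name group-by-time as the treatment test and exclude the group main effect. Leave bone height to a separate model suited to its 3-, 6- and 12-month readings.

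The cost is a short text change and one degree of freedom for the baseline covariate (37 against 38 when teeth are treated as independent). No new visits or measurements are needed.
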